### Statistical analyses

The results of this trial for primary outcomes will be analyzed based on both the intention-to-treat protocol and per-protocol datasets. SAS 9.2 software (SAS Institute Inc.) was used to generate the randomization sequence. Statistical analyses will be performed with SPSS 21.0 (IBM Corp., Armonk, NY, USA) statistical software. The continuous variables with normal distributions will be described as mean ± standard deviation, and an independent sample *t-test* will be used for difference tests. The continuous variables with non-normal distributions will be described by the median (IQR), and the Mann–Whitney U test will be used for the difference tests. The Chi-square test or Fisher’s exact test will be used for categorical data. The Chi-square test or Fisher’s exact test will be used to assess adverse events. The Kaplan–Meier method will be used to calculate survival analysis. The log-rank test will be used to compare the complication rate between the two groups, and *P* values < 0.05 will be considered statistically significant.

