**Discussion:**

Compared with the “Step-up,” the “One-step” minimally invasive surgery can significantly reduce the number of operations, reduce the length of hospital stay and hospitalization costs without increasing the incidence of composite endpoint events, and has better short- and long-term efficacy and safety. Additionally, there was no statistically significant difference in perioperative complications and mortality between “Step-up” and “One-step”. This study will assist with the formulation of an effective and scientific “One-step” minimally invasive treatment strategy for IPN, and an understanding of this technique will facilitate clinical decision-making for IPN.

*Trial Registration* ChiCTR2100044348. Trial status: Ongoing.

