### Secondary outcome

The incidence of organ dysfunction and organ function were evaluated according to the modified Marshall score.Complication: The complication rate mainly includes short-term and long-term complication rates, among which short-term complications include bleeding, gastrointestinal perforation, and pancreatic leakage. Long-term complications include incisional hernia, pancreatic endocrine and exocrine dysfunction, chronic pancreatitis, and portal hypertension. Pancreatic endocrine dysfunction was defined as HbA1c ≥ 6.5% (48 mmol/mol) and/or FPG ≥ 126 mg/dl (7.0 mmol/l) 3 months after diagnosis or pancreatitis. Pancreatic exocrine dysfunction was determined in a variety of ways including direct pancreatic function testing, measurement of fecal elastase or fecal fat levels (72 h fecal fat excretion > 7 g/d) and need for oral pancreatic enzyme replacement therapy. Chronic pancreatitis was defined as repeated upper abdominal pain; abnormal serum or urine pancreatic enzyme concentrations (lipase or amylase activity 2–3 times above the upper limit of normal); abnormal exocrine function (stool elastase < 200 µg/g) while the endosonography/CT/MRI imaging shows dilated main duct and side branches, intraductal and parenchymal calcifications[10, 11].The number of surgical procedures which includes PCD and the total number of operations.Mortality: The incidence of in-hospital death and deaths within 90 days of discharge.The length of hospital stays, the length of intensive care unit (ICU) stay, and hospitalization costs.Changes in inflammatory markers, including white blood cell (WBC), interleukin-6 (IL-6), C-reactive protein (CRP), and procalcitonin (PCT)

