### Perioperative treatment for enrolled patients

For patients who received “One-step” minimally invasive pancreatic necrotic tissue debridement, clinicians must provide symptom-based treatment, such as electrocardiograph monitoring, antibiotics, proton pump inhibitors, analgesics, octreotide, and nutrition support. Routine blood tests, serum CRP, PCT, IL-6, and arterial blood gas tests will be used to monitor delayed bleeding, incision, and/or abdominal infection after surgery. After the recovery of gastrointestinal function, a semi-liquid diet can be gradually administered until a normal diet is resumed. In addition, it is also necessary to pay attention to the characteristics of the drainage fluid in the abdominal drainage tube and be alert to delayed abdominal hemorrhage. When the amount of drainage fluid in the abdominal drainage tube is gradually reduced and the characteristics of the drainage fluid are clear, the drainage tube can be removed gradually. The patients can then be discharged from the hospital.

For patients who received “Step-up” minimally invasive pancreatic necrotic tissue debridement, clinicians provide electrocardiograph monitoring, antibiotics, proton pump inhibitors, analgesics, octreotide, and nutrition support after receiving PCD therapy. Routine blood tests, serum CRP, PCT, IL-6, and arterial blood gas tests are continued to monitor the abdominal infection. If the patient’s infection symptoms are resolved, the current therapies will be continued until normal status is achieved. If the patient’s infection symptoms are not relieved within 48 h of PCD treatment, they will undergo minimally invasive pancreatic necrotic tissue debridement. The postoperative treatment is the same as the “One-step” approach.

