## Discussion

The treatment strategy of IPN is to perform adequate debridement and drainage under the premise of basic treatment, but there are some difficulties: (1) SAP patients are often in critical condition with organ dysfunction or serious complications, and have poor tolerance for surgical trauma. Therefore, timely and effective surgical treatment is often difficult, which delays the optimal treatment. (2) Even if laparotomy is performed, due to the great trauma, more serious complications such as bleeding, intestinal fistula, diffuse abdominal infection, or multiple organ dysfunction may worsen, with an average mortality rate of 30.8% [4, 13]. In recent years, with the rapid development of minimally invasive surgery, minimally invasive techniques have been gradually applied to the surgical treatment of IPN, and the therapeutic effect has significantly improved. The current minimally invasive treatment methods primarily include ultrasound-or CT-guided PCD, endoscopic pancreatic necrosis tissue debridement, laparoscopic abdominal cavity lavage, laparoscopic pancreatic or peripancreatic necrosis tissue debridement, and video-assisted retroperitoneal necrosis tissue debridement [5, 6, 14]. The PANTER study confirmed that the minimally invasive technique is significantly better than open surgery for the treatment of IPN, especially for critically ill patients, and has been recommended by various guidelines [5, 15, 16]. At present, minimally invasive surgery for IPN mostly adopts the “Step-up” treatment strategy, that is, PCD is performed first, and minimally invasive surgery and open surgery are performed sequentially for those whose infection symptoms cannot be controlled. In our clinical experience, we have observed some problems with the “Step-up” strategy. First, is PCD treatment necessary? PCD, as a minimally invasive treatment for rapidly controlling infection symptoms and improving the patient’s overall condition, has been adopted as the first choice of initial treatment for IPN in many clinical centers. However, some patients with IPN do not require PCD therapy because they are in good condition and can tolerate surgery after active systemic support. Secondly, the “Step-up” strategy may lead to longer treatment time and increased hospitalization costs. Previous research indicates that the treatment time of PCD is typically 1–3 weeks and the total course and cost of treatment for patients who experience treatment failure will significantly increase [17, 18]. Meanwhile, some patients lack a safe puncture path for PCD treatment. In addition, PCD treatment is associated with an increased risk of abuse. Since PCD is easy to master and results in few complications, it should be noted that there is no clinical tendency to choose the PCD procedure, which may lead to increased difficulty in subsequent surgical treatment. To overcome the above shortcomings, we put forward the concept of the “One-step” strategy in China, that is, minimally invasive video-assisted debridement is directly performed for patients with IPN patients who are in relatively good general condition without PCD procedure [8].

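### The rule for non-normal variables (median and Mann–Whitney) neither tests nor estimates the average cost difference that the cost-reduction claim needs; a mean difference with a confidence interval should be added

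*Protocol article*

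**What the plan says.** The Statistical analyses section sets one rule for every continuous variable, according to its distribution. For the normal case, "The continuous variables with normal distributions will be described as mean ± standard deviation", with an independent-sample t-test. In the other case, variables with "non-normal distributions will be described by the median (IQR), and the Mann–Whitney U test will be used for the difference tests".

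The Secondary outcome section lists "The length of hospital stays, the length of intensive care unit (ICU) stay, and hospitalization costs" and attaches no separate method, so the general rule governs cost. The Discussion paragraph of the abstract anticipates that One-step can "reduce the length of hospital stay and hospitalization costs".

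Step-up has two paths (Perioperative treatment for enrolled patients). If the patient's "infection symptoms are resolved, the current therapies will be continued until normal status is achieved". If the "infection symptoms are not relieved within 48 h of PCD treatment, they will undergo minimally invasive pancreatic necrotic tissue debridement". The main Discussion adds that after PCD "the total course and cost of treatment for patients who experience treatment failure will significantly increase".

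**The concern.** Whether a strategy saves money is a question about the mean, because mean cost times number of patients is total cost. A median cannot be turned into a total. The Mann–Whitney test in effect asks whether a One-step patient is equally likely to cost more or less than a Step-up patient.

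The two questions agree when the arms differ only by a shift or a scale factor. They can part when the shapes differ, and the protocol gives a reason to expect that: some Step-up patients finish on PCD alone, while others have PCD and then debridement at higher cost. A rank test gives little weight to how expensive the second group is, although that is one of the places where the authors expect the saving to arise. The cost conclusion could then be wrong in either direction, and the planned output would contain no estimate of the saving to correct it.

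**Working it through.** **The plan's own figure.** The document has no figure for cost. Its only calculation is for the primary endpoint: 20% against 45%, one-sided α 0.05, power 80%, 20% withdrawal. The normal-approximation formula gives 42.35 per arm. With continuity correction this is (42.35/4) × [1 + √(1 + 4/(42.35 × 0.25))]² = 50.03, so 51 per arm. Then 51/0.80 = 63.75, so 64 per arm and 128 in total, as stated. It is used here only to fix the arm sizes at 51 and 64.

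**Inputs.** From the document: the analysis rule, the arm sizes, the two Step-up paths, and higher cost after PCD failure. Assumed, because the document is silent: all cost levels, spreads and shares, log-normal variation within each group, and a two-sided 5% test.

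**Why equal means and equal ranks separate.** Set mean One-step cost to 1. Let a share π of Step-up patients finish on PCD alone at mean cost L, and let M be the overall Step-up mean. The mean after PCD failure is then H = (M − πL)/(1 − π). With M = 1, π = 0.5 and L = 0.5, H = (1 − 0.25)/0.5 = 1.5. At a coefficient of variation (CV) of 0.5 the One-step median is 1/√1.25 = 0.89. The simulated Step-up median is 0.77, and a One-step patient is the cheaper of a random pair with probability 0.44. The means are equal, but the ranks favour Step-up.

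**Equal means, 64 per arm, CV 0.5, smooth One-step costs**

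| PCD-only share | L | H | Mann–Whitney rejects |
|---|---|---|---|
| 35% | 0.5 | 1.27 | about 10% |
| 50% | 0.5 | 1.50 | about 22% |
| 65% | 0.6 | 1.74 | about 32% |

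Nearly all of these rejections call One-step costlier. Welch's comparison of means rejects in 4% to 6%.

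A second parameterisation used 30% to 65% PCD failure, failures costing 2 to 4 times a PCD-only course, and log-SD 0.4 to 0.6. It gives about 6% to 77% for Mann–Whitney and again 4% to 6% for Welch.

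A wider 60-cell grid (π 0.20 to 0.65, L 0.5 to 0.9, CV 0.3 to 0.8) gives 4.4% to 76.5%, with a median of 6.1%. Of the 60 cells, 23 exceed 7% and 60 − 23 = 37 do not. The rate stays near 5% when π is 0.20 or L is 0.9.

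**True 20% mean saving by One-step (M = 1/0.8 = 1.25), 64 per arm, CV 0.5 unless stated**

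| π | L | H | Mann–Whitney | Welch |
|---|---|---|---|---|
| 35% | 0.5 | 1.65 | 20% | 50% |
| 50% | 0.5 | 2.00 | 6.7% (3.2% in the right direction) | 38% |
| 65% | 0.6 | 2.46 | 0.4% for One-step, 11.6% for Step-up | 31% |
| 35% | 1.0 | 1.38 | 68% | 69% |
| 35% | 1.0 | 1.38 (CV 0.8) | 38% | 34% |
| 35% | 1.0 | 1.38 (CV 1.2) | 24% | 19% |

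In the last three rows PCD-only patients cost as much as One-step patients, and the rank test is level or better.

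**One-step costs split as well.** Let 20% of One-step patients, the composite rate assumed in the Sample size section, cost 3 times the rest, and let Step-up failures cost 3 times a PCD-only course. Mann–Whitney then rejects in about 4% to 8% at equal means. With a true 25% saving its power is 39% to 77% against 32% to 66% for Welch, and it is the higher of the two in nearly every cell. The picture shifts again with the ratios:

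- If the One-step multiple is 2, rejection at equal means is 6% to 27% and Welch keeps more power.
- If the One-step multiple is 3 and the Step-up ratio is 2, rejection is 8% to 22%, now nearly always calling One-step cheaper.

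**The case against.** The strongest reply is that the cost pattern behind the large error rates is only partly the protocol's. The Discussion says that cost rises after PCD failure. It does not say that PCD-only patients are cheap relative to One-step. Forcing equal means creates that gap: at 30% failure and ratio 3 the PCD-only mean must be 1/(0.7 + 0.3 × 3) = 0.625 of One-step, and at 65% and ratio 4 it must be 1/(0.35 + 0.65 × 4) = 0.34. Nor is One-step free of a split. The Sample size section expects about 20% of its patients to die or have a severe complication, and the Retroperitoneal surgical approach section foresees a second operation. This stands, and it removes any claim to a known size or direction.

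Mann–Whitney also holds its level under its own null of identical distributions, so a rejection at equal means is an error only if the mean is the target. The protocol names no mean and plans no economic evaluation. Cost is one of several secondary outcomes, and an estimator for it is often left to an analysis plan. These points limit the importance. They do not remove the mismatch: the article states a rule that covers cost and also anticipates a reduction in cost, which a median and a rank p-value cannot quantify.

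A reader might go further and infer that the rank test will reject at equal means and will miss real savings, with a power loss of 20 to 57 points. That range belongs to one assumed ratio (3) with smooth One-step costs. The documents support only that these errors can occur.

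**Conclusion.** The point holds as a mismatch between analysis and claim. If costs are judged non-normal, which is very likely but not certain, the planned output gives neither a test nor an estimate of the difference in average cost. This is so whatever the true cost distributions are.

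The effect on error rates is conditional. It is large when a sizeable share of Step-up patients (about 35% or more) finish on PCD alone at clearly lower cost than One-step, and One-step costs are not themselves split. It is small or absent in much of the range examined, and its direction can reverse. The document does not give the figures needed to say which case applies. Nothing here shows that the rank test is invalid or should be dropped. The primary endpoint and the 128-patient calculation are unaffected.

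**What to change.** Add one sentence to Statistical analyses, for example: Hospitalization cost will be compared as the difference between arms in arithmetic mean cost per randomised patient, with a 95% confidence interval (bootstrap or Welch, named in advance), whatever the distribution; median (IQR) and the Mann–Whitney test will be supplementary. Base any conclusion that One-step reduces costs on that difference and its interval.

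The change uses cost data already in the case report form (Data collection) and needs no further patients. Its drawback is that the mean is more sensitive to a few very costly patients. This widens the interval, and the reader will see it there.

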### Interim analyses

Statistical analysis for the primary endpoint will be performed when the total number of enrolled patients reaches 64. The interim analysis will be carried out by an independent team of statisticians and the results will be reported to DSMC. The DSMC will have unrestricted access to all data and will discuss the results of the interim analysis and ultimately report to the Efficacy and Safety Evaluation Committee of the research group, who will determine whether the study can be continued or not. If the efficacy or safety of the “One-step” approach is lower than “Step-up” approach in the results of interim data, we will suspend the clinical trial.

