### Adverse events

All serious adverse events (SAEs) occurring between the signing of the informed consent and the end of the trial will be recorded in detail within 24 h. Subsequently, researchers will report the SAEs to the ethics committee of the unit. SAEs are defined as any damage whether associated with the anticipative outcome of the surgery or not. The study includes a data monitoring committee that will supervise the safety data in an unblinded manner in accordance with the Standard Operation Procedures for Clinical Trials. Enrolled patients will receive the best treatment available to resolve any complications.

If the incidence of treatment-related deaths or the proportion of Grade IV postoperative complications determined to be causally related to the procedure exceeds 5% of the total number of patients enrolled, the enrollment of patients must be suspended immediately. Continuation of the study will then be subject to review by the Efficacy and Safety Evaluation Committee of the research group.

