### Sample size

The sample size was calculated using PASS 11.0 (NCSS Statistical and Data Analysis, USA) software and was estimated based on the results of our center’s previous research and published literature. According to our previous studies and domestic and foreign reports, the incidence of a mixed endpoint is approximately 20% for the “One-step” approach and approximately 45% for the “Step-up” approach [8]. Using a one-sided test, the α value was equal to 0.05, and the statistical power was 80%. The withdrawal rate was expected to be 20% during the study period. Thus, this study requires at least 128 patients, with 64 patients each group.

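### Both suspension rules lack a statistical boundary: the interim rule fires on any unfavourable difference in efficacy or undefined safety, and the 5% safety rule has an unclear denominator and no minimum number

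*Protocol article*

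**What the plan says.** **Interim analyses section.** The primary endpoint is analysed once before the end, and this is "performed when the total number of enrolled patients reaches 64". An independent statistical team reports to the DSMC, which reports to the Efficacy and Safety Evaluation Committee of the research group, "who will determine whether the study can be continued or not". The next sentence sets an automatic consequence: if One-step's efficacy or safety is lower than that of the Step-up "approach in the results of interim data, we will suspend the clinical trial". The section gives no margin, P value or confidence limit. It does not say which measure stands for safety.

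**Adverse events section.** The rule counts treatment-related deaths, or Grade IV complications judged to be caused by the procedure. If either "exceeds 5% of the total number of patients enrolled, the enrollment of patients must be suspended immediately". Then: "Continuation of the study will then be subject to review by the Efficacy and Safety Evaluation Committee of the research group". No minimum number is stated, nor whether the denominator is the running or the planned enrolment.

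**Sample size section.** "the incidence of a mixed endpoint is approximately 20% for the" One-step approach and "approximately 45% for the" Step-up approach, with a one-sided α of 0.05, 80% power, 20% withdrawal and 128 patients.

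**The concern.** A rule that reacts to the direction of a difference alone, at 32 patients per arm, reacts largely to noise when the true difference is small. Joining two comparisons with 'or' adds a second chance to trip, and the second one is undefined. A trial going exactly to plan on the primary endpoint could therefore be suspended over one extra death in the One-step arm.

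The last two sentences of Interim analyses also conflict. One leaves continuation to a committee's judgement; the other makes suspension automatic. Timing by enrolment means the most recent patients have incomplete outcomes when the comparison is made.

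The 5% rule raises a similar problem. An observed proportion checked against a fixed line from the first patient onwards is very unstable early on, and the two readings of the denominator give quite different rules.

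At stake are unnecessary suspensions, and disagreement at the time about whether a trigger has been met.

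**Working it through.** **1. The plan's own figure.** Inputs from Sample size: 20% v 45%, one-sided α 0.05, power 80%, withdrawal 20%. The pooled normal formula gives 43 per arm; with continuity correction, 51. Then 51/(1 − 0.20) = 63.75, so 64 per arm and 128 in total. The stated size reproduces. With 1:1 allocation, 64 enrolled means about 32 per arm.

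**2. Interim rule, efficacy limb alone.** Let X₁ and X₂ be the composite events in One-step and Step-up, each binomial with n = 32. The limb trips when X₁ > X₂:

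P(X₁ > X₂) = Σ over i > j of P(X₁ = i) × P(X₂ = j)

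| True rate, One-step v Step-up | P(trips) |
|---|---|
| 20% v 20% | 43.8% |
| 32.5% v 32.5% | 44.7% |
| 45% v 45% | 45.0% |
| 35% v 45% | 17.1% |
| 30% v 45% | 8.3% |
| 20% v 45% (design) | 1.0% |

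Ties are not counted; with equal arms at these rates they would add 10–12 points. With only 26 per arm evaluable (32 × 0.8 = 25.6), the equal-arm figures are 43–44%.

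**3. Interim rule, both limbs.** The document does not define safety. Assumption: it means death, death is part of the composite, and mortality is equal in the two arms. By simulation with 32 per arm:

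| Composite, One-step v Step-up | Mortality, both arms | P(either limb trips) |
|---|---|---|
| 20% v 20% | 10% | 56% |
| 45% v 45% | 10% | 62% |
| 35% v 45% | 10% | 47% |
| 20% v 45% | 10% | 42% |
| 20% v 45% | 5% | 38% |

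In the last two rows almost all of the probability comes from the safety limb.

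**4. The 5% rule.** Running denominator: 1/19 = 5.26% exceeds 5%, while 1/20 = 5.00% does not, so one qualifying event among the first 19 patients is enough. P(at least one in 19) = 1 − (1 − p)¹⁹. The chance of ever crossing by patient 128 comes from an exact patient-by-patient recursion.

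Planned denominator: 6/128 = 4.7% and 7/128 = 5.5%, so 7 events are needed, with P = P(Bin(128, p) ≥ 7).

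The article gives no rate for these events, so p is assumed:

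| True rate p | ≥1 in first 19 | Running count, ever by 128 | Running, from 20 enrolled | Against planned 128 |
|---|---|---|---|---|
| 1% | 17% | 19% | 7% | 0.03% |
| 2% | 32% | 38.5% | 23% | 1.5% |
| 5% | 62% | 84% | 77% | 46% |

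**5. What a formal harm boundary would do.** Pooled z-test at 32 per arm, one-sided p < 0.01 against One-step: the false-alarm probability is 1.0% with both arms at 32.5%. The chance of detecting a true harm is 16% for 35% v 20% and 43% for 45% v 20%.

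**The case against.** The strongest reply is that, on the primary endpoint, the interim rule is close to ordinary futility stopping. At 20% v 45% it trips 1% of the time. Treated as binding, it lowers simulated power at 64 per arm only from 92.7% to 92.4%, and it does not raise the type I error. This stands for the efficacy limb. It does not cover the safety limb, nor smaller true benefits. Nor is equality far-fetched here: the abstract's Discussion speaks of benefit without any increase in composite events.

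Four stronger readings are tempting, and the document does not support them.

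- *The trial is likely to be terminated by chance.* Both rules suspend. The Adverse events section provides for review, and Interim analyses leaves continuation to a committee.
- *The look inflates the false-positive rate.* No efficacy stop is stated. Only if the look could also end the trial for success at P < 0.05 would total alpha rise, to about 8%.
- *The 5% line contradicts the 20% and 45% rates.* Those are rates of death or Clavien-Dindo IIIa and above, whatever the cause. The safety rule counts only related deaths and related Grade IV events.
- *Pooling the arms leaves harm in one arm unseen.* Three events among 64 is 4.7% overall but 3/32 = 9.4% if all fall in one arm. However, the DSMC sees unblinded data and may hold periodic and emergency reviews (Monitoring and quality assurance).

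It can also be said that boundaries belong in a DSMC charter or SAP. That would excuse silence. Here the article states operative triggers and consequences, and these are what need changing.

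**Conclusion.** The concern holds for the rules as written. The interim rule has no margin and an undefined safety limb, and its automatic consequence must be reconciled with the committee decision stated just before it. Its efficacy limb trips 44–45% of the time under equality, 17% at 35% v 45% and 1% at the design rates. The combined figures, 56–62% under equality and about 42% at the design rates, rest on reading safety as death with 10% mortality in both arms; 5% mortality gives 38% at the design rates.

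The 5% rule has two defensible readings with very different behaviour: 38.5% against 1.5% at an assumed true rate of 2%, and 84% against 46% at 5%. The word 'immediately' favours the running count, but the text does not settle it.

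The consequence is avoidable suspension and dispute over whether a trigger has been met. It is not a demonstrated loss of alpha control or certain termination.

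**What to change.** **Interim analyses.**
- Replace the directional trigger with a preset, non-binding boundary that guides the DSMC, applied to the primary endpoint and to one named safety measure.
- Choose its level only after tabulating false-alarm and harm-detection probabilities together. One-sided p < 0.01 gives about 1% false alarms but detects 45% v 20% harm only about 43% of the time, so it should not be adopted by default.
- Hold the look when 64 patients have a completed primary outcome.
- State that there is no efficacy stop, or give an alpha-spending boundary.
- Reconcile the automatic suspension with the committee's decision.

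**Adverse events.**
- State the denominator and a minimum number.
- Use a sequential boundary, reported by arm, with a stated false-alarm probability.
- The sponsor and DSMC set the acceptable event rate.

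**Cost.** Protocol and charter wording, and a somewhat later interim look. A modest harm may be flagged later by the formal rule than by a bare comparison, so the DSMC's periodic and emergency reviews should be kept explicitly as the safeguard.
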